**8. Data Gathering Activity 2: School Mapping**

**a. Subject Population**

- The study population is all public primary schools in Wajir County, all primary schools in Nairobi County where program girls are attending, and secondary schools in both counties where program girls enrol during the study period.

**b. Research Protocol**

- Prior to the start of the baseline survey, the Council will engage an independent consultant to conduct a mapping exercise to locate all public primary schools in Wajir County and map them using GPS coordinates. The Ministry of Education, Science and Technology will be engaged to provide support for the exercise in exchange for receiving access to the data. While conducting the mapping, a school quality survey (see Annex 3) will be completed that collects basic indicators on a school – including but not limited to teacher-student ratio, public v. private, number of female teachers, and the presence/type of latrines. These quality measures will later be accounted for in the analysis as a mediating factor in the relationship between the intervention and schooling outcomes. The survey will include observation of school facilities and questions about the school that will be answered by the school administrator.
- The school mapping activity will take place in October, 2014 in Wajir and in May, 2015 in Nairobi and will be conducted by an independent consultant.
- In Nairobi, once girls are invited to participate in the study, a list of the schools they are attending will be generated and the school quality survey will be completed on each school.
- In both Nairobi and Wajir, a school quality survey will also be completed for any secondary schools that the girls enrol in during the two-year study period.

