3. Kits: at the start of each term, a girl will receive a schooling kit with the following items: 4 packs of sanitary towels, 2 panties, 1 small container of petroleum jelly, 1 bar of soap, 1 exercisebook, 1 pencil, 1 pen. The kit follows the same conditioning rules as the school fees.
4. School Incentive: In addition to the fees, each school will receive a top-up of 500 KES/ per girl enrolled in the CCT programme. This will be paid together with the fees payments at the start of the term.

Figure 2. AGI-K Education Cash Transfer Payment Schedule

In April 2015, eligible households will register for the cash transfer programme, providing details about the girl, school, and will provided with the payment details. At the time of registration, parents/guardians will also participate in a sensitization session about the importance and value of girls’ education. A household/girl will be eligible for the CCT for the entire two year period, regardless if she met the conditions the term before (e.g. she could receive the transfer during the first period of the term, but not the second if her attendance levels drop).

Cash transfer payments to the household will be made via Equity Bank. In Wajir, the payments will use the same infrastructure as the Hunger Safety Net Programme (HSNP), through which all households in Wajir have completed paperwork for account opening with Equity Bank. In Nairobi, the payments will use the Orphans and Vulnerable Children infrastructure – a cash transfer programme through which recipients have accounts with Equity Bank that operate special wallets to receive and transact with the transfer. Households that already have Equity accounts can have the payment wallet added to those accounts. Those that do not will be facilitated to open Equity accounts at the time of registration into the education CCT.

1. Health

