- All eligible girls who consent to the interview will be interviewed at baseline. Once the survey is complete, clusters (Wajir) and households with eligible girls (Nairobi) will be randomly assigned to study arms during a public lottery. In Wajir, there is a risk of unequal distribution of clans across study arms, despite randomization. Information on clans will be collected during the school mapping exercise that can be used to stratify by clans, if necessary. Once randomization is completed, girls will be invited to participate in the various components of the programmes, based on their assigned study arms. Mentors and other programme staff will visit the girl in her home and discuss the benefits of the programme with both the girl and her mentor. They will then invite the girl to participate in the programme, obtain the necessary consents and follow-up with the girl to ensure that she has enrolled in programme activities.

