**b. Research Protocol**

- The baseline survey will be conducted between January and March, 2015, before intervention activities take place. This period was chosen to avoid the holiday months of December and April, when families are likely to travel upcountry or to visit relatives. This also avoids the rainy seasons in Wajir of October through December and April through June.
- Trained interviewers will be grouped into teams of 8-10, each team with a supervisor to provide directly quality assurance at the time and location of interviewing. The data manager and study coordinator will be in the field during data collection, reviewing the quality of the surveys on a daily basis, addressing trouble areas, and sending the data to the investigators on a daily basis for review. Once respondents have been randomly selected, interviewers will visit households to conduct the interview with selected respondents. If the respondent is not present at the household on the day of the interviewer visit, the interviewer will pay at least three visits to the household in order to locate and interview the selected respondent, similar to the procedure used in the Demographic and Health Surveys (DHS). No replacement will be undertaken, so as not to bias the sample toward ‘stay-at-home’ respondents. Before the surveys are conducted, informed consent will be obtained from parents/guardians of girls, and from girls themselves. Parental consent will not be required from emancipated minors (e.g. married girls) and girls of the age of 18 or older (during the endline survey). To the extent possible, interviews will be conducted in a private area, with visual and auditory privacy.
- Survey instruments (see Annex 4) will be implemented by electronic data capture: Computer-Assisted Personal-Interviewing (CAPI) on tablet computers. CAPI is a process of data capture in which the interviewer reads the question from a computer screen and enters the participant’s response directly into a handheld or tablet device.

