**APPENDIX C: AGI-K Timeline**

| **Timeline:** |  |  |
| --- | --- | --- |
|  | **JANUARY 2014** | Start of Inception Phase |
|  | **OCTOBER 2014** | Start of Implementation Phase |
|  | **JANUARY - MARCH 2015** | Baseline Survey data collection |
|  | **APRIL - JULY 2015** | Start of intervention |
|  | **APRIL 2016** | Midterm Implementation Report |
|  | **JULY - AUGUST 2016** | Qualitative Data collection |
|  | **MARCH - JUNE 2017** | End of intervention |
|  | **APRIL - OCTOBER 2017** | Midterm Survey data collection |
|  | **MARCH 2018** | Midterm evaluation report |
|  | **APRIL - MAY 2018** | Qualitative Data collection |
|  | **APRIL – OCTOBER 2019** | Endline Survey data collection |
|  | **MAY 2020** | Final evaluation report |

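### School quality is labelled a mediator, but the Wajir primary-school score is fixed before the lottery and secondary-school scores exist only for girls who progress

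*Protocol*

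**What the plan says.** The Protocol, section 8, Data Gathering Activity 2 (School Mapping), b. Research Protocol, gives the quality survey one analytic role: "These quality measures will later be accounted for in the analysis as a mediating factor in the relationship between the intervention and schooling outcomes". That sentence closes the description of the Wajir mapping, which begins: "Prior to the start of the baseline survey, the Council will engage an independent consultant to conduct a mapping exercise". The dates follow: "The school mapping activity will take place in October, 2014 in Wajir and in May, 2015 in Nairobi". For both counties it adds that "a school quality survey will also be completed for any secondary schools that the girls enrol in during the two-year study period".

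Activity 3 (Baseline Survey) fixes the order of events. On the survey: "The baseline survey will be conducted between January and March, 2015, before intervention activities take place". On allocation: "Once the survey is complete, clusters (Wajir) and households with eligible girls (Nairobi) will be randomly assigned to study arms during a public lottery". The timeline in Appendix C puts the entry "Start of intervention" at April to July 2015.

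The education package could reach schools in two ways. Fees are paid to the school for each girl, and "each school will receive a top-up of 500 KES/ per girl enrolled in the CCT programme" (Intervention section, conditional cash transfer). Appendix D lists mean grade and primary completion as the education indicators. Activity 8 (Monitoring Data) makes the analysis intention to treat.

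**The concern.** A mediator has to be able to change with the treatment, so it must be measured after treatment has begun. A variable recorded once, before allocation, can predict the outcome or modify the effect, but it cannot carry the effect. Reporting part of the Wajir schooling effect as running through school quality would therefore be a claim that the data cannot support.

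The later measures raise the opposite problem. They come after allocation, so they could mediate. But secondary-school quality is observed only for girls who reached secondary school. A model of grade or completion that includes it either drops the other girls or conditions on something close to the outcome, and the comparison is then no longer between the randomised groups. For Nairobi primary schools the same applies only in part: where the intervention changed which school a girl attended, or whether she was in school at all by May 2015.

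**Working it through.** The Protocol gives no figure on this point, so there is none to reproduce. The check has two parts: the order of dates, and simulations whose effect sizes are all assumptions.

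**Order of dates**

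| Event | Wajir | Nairobi |
|---|---|---|
| Primary-school quality survey | October 2014 | May 2015 |
| Baseline survey | January to March 2015 | January to March 2015 |
| Lottery | after baseline | after baseline |
| Cash-transfer registration | April 2015 | April 2015 |
| Intervention starts | April to July 2015 | April to July 2015 |
| Secondary-school quality survey | schools entered during the two years | schools entered during the two years |

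The overview table in section 7 gives October to December 2014 for school mapping without separating the sites. For Wajir, either date precedes the baseline survey.

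**A. Wajir score, measured before the lottery.** Inputs: 20 v 20 clusters (80 clusters over four arms, Background section) and 40 girls per cluster (3,200/80). Cluster mean = 0.30T + bQ + cluster error (SD 0.3) + sampling error (SD 1/√40), where T is treatment and Q the standardised quality score, independent of T by randomisation. 4,000 runs.

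| Slope b | Unadjusted effect (SE) | Adjusted effect (SE) | Indirect effect, mean (SD) |
|---|---|---|---|
| 0.2 | 0.30 (0.123) | 0.30 (0.108) | 0.00 (0.067) |
| 0.5 | 0.30 (0.193) | 0.30 (0.109) | 0.00 (0.159) |

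The SD of the indirect effect is roughly b × √(2/20): 0.2 × 0.316 = 0.063 and 0.5 × 0.316 = 0.158, close to the simulated values. It is the sampling error of the arm difference in Q and nothing more. That difference was significant in about 5% of runs, as chance predicts. Adjustment left the estimate at 0.30 and reduced its SE.

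**B. Quality of a school that can change after the lottery.** Inputs: 598 girls per arm (2,394/4). Q = aT + 0.5U + error and Y = 0.30T + 0.2Q + gU + error, where U is an unmeasured cause of both school quality and outcome. 1,000 runs. The true total effect is 0.30 + 0.2a and the true direct effect is 0.30. With g = 0.5 the expected adjusted coefficient is 0.30 − 0.5 × (0.5/1.25) × a = 0.30 − 0.2a.

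| Shift a | True total | Adjusted, g = 0 | Adjusted, g = 0.5 |
|---|---|---|---|
| 0 | 0.30 | 0.302 | 0.299 |
| 0.2 | 0.34 | 0.298 | 0.258 |
| 0.4 | 0.38 | 0.303 | 0.224 |

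With no shift there is no bias. With a shift and a shared cause, the adjusted coefficient falls below both the total and the direct effect.

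**C. Secondary-school quality, observed only for girls who enrol.** U drives enrolment (correlation 0.7 with the latent tendency to enrol) and the outcome (coefficient 0.5). The treatment has no effect on the outcome.

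| Enrolment, comparison v intervention arm | Difference among enrolled girls (truth 0) |
|---|---|
| 30% v 30% | 0.00 |
| 30% v 40% | -0.07 |
| 30% v 50% | -0.13 |

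The arm that brings in more girls looks worse because it includes girls with lower U.

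**The case against.** Three points on the other side have force.

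First, a reader might infer that adjusting for school quality biases the schooling effects everywhere. The documents do not support that. The Wajir score precedes allocation, and part A shows adjustment to be harmless and useful. The measures for which adjustment can bias are the later ones, and those could legitimately mediate under stated assumptions.

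Second, a reader might infer that Nairobi primary schools were chosen after the lottery. The Protocol shows only that they were surveyed after it, from a list of schools then attended. The programme's first term is the second term of the school year, so many girls may have enrolled before allocation. Only secondary schools are shown to be entered afterwards.

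Third, a reader might infer that the main education result will be biased. The Protocol sets intention to treat and nowhere says that those effects will be adjusted for school quality. The mediator sentence follows the Wajir mapping, the secondary-school survey is given no separate analytic role, and the mediation model may be in an analysis plan not shown. The bias is therefore conditional on a model that the Protocol does not state.

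It can also be said that the quality of the school a girl attends might change even though each school's score is fixed, because all Wajir public primary schools are surveyed and the scores are linked to survey data. That is true, but it would capture a change of school. It would not capture improvement of a school through the per-girl top-up.

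These points narrow the concern. They do not rescue the mediator label for the Wajir score, which is stated in the Protocol and is not a detail left for later.

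**Conclusion.** The point holds in limited form. The Wajir primary-school score precedes the lottery and is not described as repeated, so a school's score cannot carry the intervention effect, and a mediated share through it would reflect chance imbalance. This conclusion rests on the dates alone. The spread of 0.07 to 0.16 around zero rests on the assumed slopes and error variances.

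Secondary-school quality is observed only for girls who enrol after the lottery. Conditioning the schooling effect on it could bias that effect, by -0.07 or -0.13 in the assumed scenarios. The same holds for Nairobi primary-school quality only where the intervention changed the school attended or whether a girl was in school by May 2015. Part B shows no bias when quality does not shift.

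Coverage by arm is also unclear. The School Mapping section refers to Nairobi schools attended by programme girls. Activity 8 describes girls in the violence-only arm as not directly participating, so it is not stated whether their schools, or those of the external control, are surveyed. No intention-to-treat result is shown to be wrong.

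**What to change.** In section 8, School Mapping, b. Research Protocol:

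- For the Wajir primary-school measure taken before the lottery, replace the mediator label with baseline covariate and pre-stated effect modifier. Using the catchment school's score gives every girl in a cluster a value, including girls out of school.
- Add that intention-to-treat schooling effects are neither adjusted for nor restricted by the quality of schools entered after the lottery, including all secondary schools.
- State that any mediation analysis is exploratory and uses only measures taken after randomisation, with the same coverage in all arms and its assumptions written down.

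The May 2015 Nairobi score should not simply be relabelled as baseline: a girl who had moved, or was out of school by then, may have no score for the school she reported at baseline.

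The cost is a few sentences. The first two changes need no new data. The third may need wider school coverage if a mediation analysis is pursued. The downside is that the Wajir mediation claim is dropped; in exchange the score can improve precision.

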**c. Risks and Benefits to Subjects**

- There is no risk to the school or to administrators in providing this information. The questions will be standardized to those collected by the Ministry of Education, Science and Technology for their Education Management Information System, which will be publicly available.
- The benefit of participating in the exercise is that the schools in eligible study sites will benefit directly if the catchment area is randomized to receive the education intervention. The Ministry of Education in Wajir County will benefit from having a map of public primary schools, and information on the quality of these schools.

**d. Steps to Minimize Risks**

- N/A

**e. Confidentiality**

- Basic information on schools will be made available to the Ministry of Education, Science and Technology and may be made publicly available or distributed to other interested parties.
- The school quality information will be linked to survey data and no identifying information will be used in papers or conferences.

**f. Compensation**

- No compensation will be provided.

**g. Informed Consent Process**

- This activity involves gathering basic indicators for schools in the region. No personal information about individuals will be collected, but data on number of students and the profile of the faculty will be reported in aggregate.  As such we are not seeking informed consent. However, we will ask for permission from a school administrator to gather this information after providing him/her with information about the purpose of the study.

**8. Data Collection Activity 3: Baseline Survey of Adolescent Girls**

**a. Subject Population**

- The study population is girls between the ages of 11 to 14 residing in Nairobi slums or in school-catchment areas in Wajir. The participants for the baseline survey will be 3,200 girls between aged 11 to 14 in Wajir and 3,750 girls in the same age group in Nairobi (3,000 girls in the intervention sites and 750 girls in an external control site). In addition, in each household, the parent/guardian who provides consent for the girl to participate in the survey will also participate in a short interview on the household characteristics (3,200 parents/guardians in Wajir and 3,750 parents/guardians in Nairobi).
- For the Nairobi study, a household listing will be conducted to identify all girls in the target age group. The listing form will collect basic household-level data that will be used to rate households using a vulnerability index. We will select an indicator that provides adequate variation and is able to identify girls who are most vulnerable. Possible indicators include having a head of household with no education, or being behind in schooling vis-à-vis one’s age. Based on the selected vulnerability index, households of high socio-economic status (SES) will be excluded and all other households with an eligible girl between the ages of 11 and 14 will be eligible for the study.

For the Wajir study, school-catchment areas will be identified through a school-mapping activity. All catchment areas in study sites will be eligible for the project (approximately 80 total). Within these catchment areas, data from the HSNP will be used to provide the sampling frame. All girls between the ages of 11 and 14 during the time of the survey, residing in school-catchment areas within study sites will be listed from this data and households will be randomly selected for the baseline interview.

- All eligible girls who consent to the interview will be interviewed at baseline. Once the survey is complete, clusters (Wajir) and households with eligible girls (Nairobi) will be randomly assigned to study arms during a public lottery. In Wajir, there is a risk of unequal distribution of clans across study arms, despite randomization. Information on clans will be collected during the school mapping exercise that can be used to stratify by clans, if necessary. Once randomization is completed, girls will be invited to participate in the various components of the programmes, based on their assigned study arms. Mentors and other programme staff will visit the girl in her home and discuss the benefits of the programme with both the girl and her mentor. They will then invite the girl to participate in the programme, obtain the necessary consents and follow-up with the girl to ensure that she has enrolled in programme activities.

**b. Research Protocol**

- The baseline survey will be conducted between January and March, 2015, before intervention activities take place. This period was chosen to avoid the holiday months of December and April, when families are likely to travel upcountry or to visit relatives. This also avoids the rainy seasons in Wajir of October through December and April through June.
- Trained interviewers will be grouped into teams of 8-10, each team with a supervisor to provide directly quality assurance at the time and location of interviewing. The data manager and study coordinator will be in the field during data collection, reviewing the quality of the surveys on a daily basis, addressing trouble areas, and sending the data to the investigators on a daily basis for review. Once respondents have been randomly selected, interviewers will visit households to conduct the interview with selected respondents. If the respondent is not present at the household on the day of the interviewer visit, the interviewer will pay at least three visits to the household in order to locate and interview the selected respondent, similar to the procedure used in the Demographic and Health Surveys (DHS). No replacement will be undertaken, so as not to bias the sample toward ‘stay-at-home’ respondents. Before the surveys are conducted, informed consent will be obtained from parents/guardians of girls, and from girls themselves. Parental consent will not be required from emancipated minors (e.g. married girls) and girls of the age of 18 or older (during the endline survey). To the extent possible, interviews will be conducted in a private area, with visual and auditory privacy.
- Survey instruments (see Annex 4) will be implemented by electronic data capture: Computer-Assisted Personal-Interviewing (CAPI) on tablet computers. CAPI is a process of data capture in which the interviewer reads the question from a computer screen and enters the participant’s response directly into a handheld or tablet device.
- Due to the longitudinal nature of the study, it is important to ask all girls basic information on experience of marriage, female circumcision, violence and sexual intercourse. This data will provide the baseline for examining changes in the program indicators over time (see Appendix D). Since many of the respondents are unlikely to have experienced these events at the study age (11 to 14), they will be skipped out of answering additional questions once they indicate that they have never experienced each event. Some sections on sexual behaviour, intimate-partner violence and family planning will only be asked of those who have been married or have had sex, particularly for Wajir where sex generally occurs within the context of marriage.

